### Screening and randomization

2.6

Participant recruitment will take place using a flyer in local media, at the study sites and at the supporting partner organization, German Multiple Sclerosis Society (DMSG) (Hannover, Germany). Subsequently, interested candidates can contact the scientific study team via telephone or email. An initial telephone interview will be conducted using a standardized script, where eligibility is checked according to the inclusion and exclusion criteria. Inclusion and exclusion criteria are similar to the criteria in the MS-HIPPO study and can be seen in Table 3, Table 4 [14]. If an inclusion is possible, patients will subsequently be referred to a study site physician, who will carry out an initial examination and approve a medical clearance. The patients included, will be informed about the study protocol and asked for their written consent. Patients can withdraw from the study at any time; medically relevant withdrawals are forwarded to the monitor and responsible ethics committee. After initial contact, written informed consent and medical clearance of the participants, they will be randomly assigned to IG and CG. The allocation sequence will be generated by computer-generated random numbers. Individuals are randomized stratified by location, gender distribution of the disease and Expanded Disability Status Scale (EDSS) [34]. A code-generated random mechanism will be used for concealment. Scientific study personnel will generate the allocation sequence, enroll participants, and assign participants to interventions based on a stratified adaptive randomization.

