**Methods:**

Based on a prospective, randomized, investigator-blinded, controlled multicenter study design, the primary endpoint of differences in balance will be investigated. Patients will be randomized to an intervention group (12 weeks of hippotherapy) or a control group (12 weeks of treatment as usual). Balance will be measured using the Berg Balance Scale (BBS) plus a standardized balance task on a force plate (AccuGait-Optimized, Advanced Mechanical Technology, Inc., Massachusetts, US) and a balance perturbation task on an oscillating sensorimotor therapy device (Bioswing Posturomed®, Haider, Pullenreuth, Germany). During balance tasks, electrocortical activity will be investigated using electroencephalography (EEG) (LiveAmp 32, Brain Products GmbH, Gilching, Germany). Secondary endpoints include fatigue (FSS), quality of life (MSQoL-54), pain (VAS), spasticity (NRS) and participation (WHODAS 2.0). Therapy progress will be documented via an ICF-based hippotherapy assessment-tool (EQUITEDO®, Frechen, Germany).

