### Study population

2.3

Inclusion and exclusion criteria for participants are shown in Table 3, Table 4. Participants will be asked not to change or interrupt their existing physiotherapy or pharmacotherapy, e.g. their treatment as usual, during the data acquisition timeline. Written informed consent from participants will be obtained by a scientific study team.

**Table 3 tbl3:** Requirement profile participant inclusion.

Inclusion criteria
Confirmed multiple sclerosis with spasticity of the lower limbs (all phenotypes)
Expanded Disability Status Scale (EDSS) score between 4 and 6
Written informed consent of the patient
Consent of the study site physician
Legal competency
Minimum age of 18 years

**Table 4 tbl4:** Requirement profile participant exclusion.

Exclusion criteria
Hippotherapy within the last 12 months
Parallel participation in other intervention studies
Persons, who are in a dependent/employment relationship with the sponsor or investigator (potential conflict of interest)
Body weight over 90 kg
Acute exacerbation of the disease four weeks before the start of therapy
No balance while sitting
Planned start of treatment with new antispastic medication or with medication that may have an influence on test parameters (examples: Nabiximols (Sativex®), neuraxial administration of baclofen; 4-aminopyridine)
Seizure disorder not controlled by medication
No or insufficient ability to spread the legs so that the patient can sit on the horse
Known severe osteoporosis
Known severe osteoarthritis of the hip
Known severe scoliosis that could be aggravated by hippotherapy
Severe blood clotting disorders where there is a risk of hematoma due to hippotherapy
Insufficiently stable concomitant diseases in the field of internal medicine, gynecology and/or surgery
Allergy to horse hair
Pregnancy
No balance impairment (Berg Balance Scale over 50 points before the start of the intervention)

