### Outcomes

2.5

The primary endpoint of the study is the change in balance performance after 12 units of hippotherapy (change from baseline). To assess the primary outcome measure, the Berg Balance Scale (BBS) will be used in an independent assessment by a blinded observer (Table 5). Blinded assessors will be trained for collecting the BBS data prior to the start of the intervention by the investigators. Unblinding is not permitted during the trial. Assessors will be trained to collect EEG, force plate and Posturomed® data. Therapists at study centers will be educated and instructed on how to complete Adverse Event Report forms (AEs) and EQUITEDO® assessments.

**Table 5 tbl5:** Protocol Berg Balance Scale.

(0–4 points/sum score)
1. from sitting to standing
2. standing without support
3. sitting without support
4. from standing to sitting
5. transfers
6. standing with eyes closed
7. standing with feet close together (close foot stance)
8. reaching/longing forward with outstretched arm
9. picking up an object from the floor
10. turn around to look backwards
11. turn 360°
12. alternately place your feet on a footrest
13. standing with one foot in front of the other (tandem stand)
14. standing on one leg (one-legged stand)

As the gold standard for measuring balance in a clinical setting, the BBS enables the results of this therapy to be compared with other interventions, and is therefore applied as primary outcome measure [18,19]. In regard to validity and reliability, the BBS shows satisfactory values [[18], [19]].

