### Assessment

2.7

At baseline, post and follow-up, balance performance, BBS, EEG, quality of life, fatigue, pain, spasticity and activity- and participation-related parameters will be collected. The following table (Table 7) shows the time schedule of patient enrolment and intervention.

**Table 7 tbl7:** Time schedule.

	Registration	Baseline assessment	Post assessment	Follow-up assessment
Fulfillment of the inclusion criteria	X	12 weeks hippotherapy or 12 weeks treatment as usual		6 weeks treatment as usual
Written declaration of informed consent	X			
Medical clearance	X			
Assignment to the study group	X			
Anthropometric data	X			
Balance assessment/EEG		X	X	X
BBS		X	X	X
Quality of life (MSQoL-54)		X	X	X
Fatigue (FSS)		X	X	X
Pain (VAS)		X	X	X
Spasticity (NRS)		X	X	X
WHODAS 2.0 36-Self		X	X	X
EQUITEDO® (IG only)		X	X	

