
The secondary study endpoints will be examined using descriptive statistical methods. Furthermore, to complement the primary analysis, an analogous ANCOVA will also be performed for secondary study endpoints. For the quality of life questionnaire (MSQoL-54), an MCID of 1.5 and 2.5 points will be applied [39]. Three procedures are applied to analyze the study results: (1) the *modified* intention-to-treat population (*m*ITT), which comprises all registered patients who completed the pre-measurement and serves as the primary analysis set for this investigation. It represents a solution for managing complications as noncompliance or missing outcomes and therefore reflects the practical clinical scenario [40]. (2) The *per protocol* population (PP): This data set contains all patients who completed the study without or with very minor violations of the regulations according to the study program and is considered a sensitivity analysis. It is considered a protocol violation if less than 9 units of hippotherapy were completed. Analyses for primary and secondary endpoints will be conducted for *m*ITT and PP populations, whereas evaluations based on the PP-population will serve as sensitivity analyses. (3) The third data set includes the safety population and considers AEs; it includes patients who completed at least one treatment, as opposed to the treatment they were randomized to receive. Safety data (AEs) are summarized and documented according to type, severity, intensity and correlation [41].

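### Group assignment precedes the baseline visit, yet the primary analysis set keeps only patients who completed that visit, so losses between the two drop out of the primary analysis

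*Protocol article*

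**What the plan says.** **Order of events.** Section 2.6 of the protocol article puts randomisation directly after consent and clearance: "After initial contact, written informed consent and medical clearance of the participants, they will be randomly assigned to IG and CG". In Table 7 (section 2.7) the row "Assignment to the study group" is marked under Registration only. The text of that section gives the time points for the outcomes: "At baseline, post and follow-up, balance performance, BBS, EEG, quality of life, fatigue, pain, spasticity and activity- and participation-related parameters will be collected". Table 7 marks none of these measures at Registration.

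**Eligibility.** Table 4 excludes patients with "No balance impairment (Berg Balance Scale over 50 points before the start of the intervention". Table 7 marks fulfilment of the inclusion criteria at Registration.

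**Primary analysis set.** Section 2.8 defines the mITT population as the one "which comprises all registered patients who completed the pre-measurement and serves as the primary analysis set for this investigation".

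**Blinding.** The abstract describes a "prospective, randomized, investigator-blinded, controlled multicenter study design". For the BBS, section 2.5 adds that it "will be used in an independent assessment by a blinded observer". Table 7 also schedules the EQUITEDO assessment at baseline for the intervention group only; section 2.5 has the site therapists complete it.

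**The concern.** Randomisation protects the comparison of all patients who were randomised. Once entry to the analysis set depends on something that happens after assignment, the protection holds only if that event is unrelated to the arm. Here the event is attendance at the baseline visit. Patients answer a recruitment flyer, and those assigned to control continue usual care, with five hippotherapy sessions offered only after the study. If they learn their arm before baseline, some may not come. They would leave no trace in the primary analysis. The linear mixed models planned as sensitivity analyses accommodate missing data under missing at random, but they cannot recover a patient who is outside the set.

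There is a smaller, second issue. Fatigue, quality of life, pain, spasticity and participation are rated by the patients themselves. If the baseline rating is given with the arm known, it is no longer a clean pre-randomisation covariate for the ANCOVA planned for these endpoints.

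**Working it through.** The point turns on the order of events, so the sections come first and the arithmetic is illustration only.

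**1. Which measurements precede assignment?**

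| Item | Where it is placed | Relative to assignment |
|---|---|---|
| Anthropometric data, consent, medical clearance | Table 7, Registration | same column |
| Location, gender, EDSS | Section 2.6, stratification factors | must be known before |
| BBS, balance tasks and EEG | Table 7, Baseline | after |
| FSS, MSQoL-54, VAS, NRS, WHODAS 2.0 | Table 7, Baseline | after |
| EQUITEDO, intervention group only | Table 7, Baseline | after |

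Section 2.1 says only that assignment comes before therapy, which fits this order. Of the covariates in section 2.8 (facility, gender, age, EDSS, baseline BBS), only baseline BBS is first measured after assignment.

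**2. Can the BBS > 50 criterion be settled before assignment?** Section 2.6 names a telephone interview and a physician's examination before assignment. Neither is said to include a BBS, and the scale needs observed performance. The only pre-intervention BBS in the schedule is the baseline one. Table 4 and Table 7 therefore do not fit together as written.

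**3. Is allocation known at baseline?** The intervention-only EQUITEDO at that visit implies that site therapists know the arm by then. No section says when patients are told, and none says that the information is held back.

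**4. Illustration of the loss (all loss rates assumed).** With 70 patients per arm, a 3% loss is 0.03 × 70 = 2.1 in the intervention group. A 10–15% loss is 0.10 × 70 = 7 to 0.15 × 70 = 10.5 in the control group.

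**5. What that could do to the BBS estimate.** Let p be the share of an arm lost before baseline, and d the amount by which the absent patients' mean BBS change would have differed from that of the patients present. The arm mean over all randomised patients equals the mean of those present plus p × d. The error in the treatment difference is then p(CG) × d(CG) − p(IG) × d(IG). Take d = 3 points, the MCID in section 2.8, purely as a yardstick:

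- same direction in both arms: (0.10 − 0.03) × 3 = 0.21 to (0.15 − 0.03) × 3 = 0.36 points;
- opposite directions: (0.10 + 0.03) × 3 = 0.39 to (0.15 + 0.03) × 3 = 0.54 points.

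**6. Self-reported baselines (shift assumed).** If knowing the arm moves one arm's baseline by 0.2 SD and leaves the later score unchanged, a change-score comparison moves by 0.2 SD. An ANCOVA estimate moves by slope × 0.2 SD: 0.5 × 0.2 = 0.10 SD to 0.8 × 0.2 = 0.16 SD. The direction is not known in advance.

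**7. Numbers left for analysis.** The plan's own inflation is reproduced: 111 ÷ (1 − 0.20) = 138.75, so 139, taken to 140. Section 2.8 calls the 20% attrition and does not say whether it covers losses before baseline. If it does not, and a further 5%, 10% or 20% were lost there (assumed), then 133, 126 or 112 would enter the mITT set. After 20% attrition 106.4, 100.8 or 89.6 would remain, against the 111 required.

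**The case against.** The best defence is that the order alone does not bias the primary endpoint. Much of that stands.

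- A reader might infer that patients are unmasked at baseline. The documents do not say so. The EQUITEDO row shows therapist knowledge at most. The supportable statement is that nothing keeps the arm from patients before baseline.
- A reader might infer that excluding randomised patients with BBS > 50 breaks the comparison. It is a fixed cut-off on a pre-treatment score rated by a blinded observer, so it does not depend on the arm by construction. Its main effect is to lose randomised patients. The examination before assignment could also include a BBS that a condensed article does not mention; that is a reason to reconcile the sections, not to assume an error in conduct.
- A reader might infer that every baseline value is affected. Anthropometric data share the Registration column with assignment, and location, gender and EDSS must precede it. The blinded rating also protects the BBS baseline itself.
- The five sessions offered to controls after completion may limit differential non-attendance.
- The self-report argument reaches secondary endpoints only, which are described and given a complementary ANCOVA.

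None of this answers the remaining point. Blinded rating does not govern who attends, and the primary set is defined by attendance. That definition is stated in the article; it is not a detail left to a fuller document.

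**Conclusion.** The point holds in a limited form. By the article's own schedule and definition, membership of the primary analysis set is decided after randomisation, and losses between assignment and baseline would go unseen in the primary analysis. The self-reported secondary baselines are exposed if patients know their arm. The BBS > 50 criterion and Table 7 must be reconciled.

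The size of any bias is unknown. Under the assumed loss rates and a 3-point difference between absent and present patients, the BBS contrast would be off by about 0.2 to 0.5 points, which is 7% to 18% of the 3-point MCID (0.21 ÷ 3 to 0.54 ÷ 3). With equal loss in both arms and absent patients who differ alike, the error is zero. The documents do not support a claim that the trial's comparison is already compromised. They do support closing a gap that costs little to close.

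**What to change.** 1. In section 2.6 and Table 7, move assignment to after the baseline BBS screen and the questionnaires. If scheduling forbids this, withhold the result from patients and site staff until both are complete. In either case start the intervention-only EQUITEDO after that point.
2. State at which visit the BBS for the Table 4 criterion is taken, so that Table 4, section 2.6 and Table 7 agree.
3. Define the primary set in section 2.8 as all randomised patients, analysed as randomised. With the new order each of them has a baseline.
4. For patients already assigned (the project period began in January 2024), report by arm how many were lost, and how many were excluded for BBS > 50, between assignment and baseline. Add a sensitivity analysis of all randomised patients. Those with no BBS at all contribute nothing to a mixed model, so it needs imputation under stated assumptions, varied by arm.

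Cost: an amendment to one table and two sections. Some baseline visits will be spent on patients found ineligible, and therapy slots are confirmed later. For patients already assigned, only item 4 helps.

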### Design

2.1

A randomized controlled trial design will be applied to obtain data from in total 140 subjects: (1) hippotherapy intervention group (IG) (approx. N = 70) and (2) control group (CG) (approx. N = 70). Within a project duration of two years and six months (01.01. 2024–30.06. 2026), both groups, IG and CG, are to be assessed during two separate study cycles with IG (N = 35) and CG (N = 35) in each study cycle. Each study cycle will consist of a twelve-week intervention period (1x hippotherapy/week) with a pre/post measurement and a six-week follow-up measurement (see Fig. 1). Before therapy begins, the population will be randomly and evenly assigned to one of two groups: IG or CG.

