### Study sites

2.2

The study will be conducted at 8 study sites in Germany (see Table 1). Hippotherapy is carried out according to the methodology of the German Curatorship of Therapeutic Riding e.V. (DKThR), which ensures quality of therapeutic measures, animal welfare and standardization [15]. All facilities fulfill the requirements for study sites shown in Table 2 and are certified facilities for hippotherapy (DKThR)® by DKThR.

**Table 1 tbl1:** Study sites.

Study sites
Center for Therapeutic Riding Johannisberg e.V., Windhagen
Center for Horseriding and Equine assisted Therapy, Carolinenhof, Essen
Center for Therapeutic Riding, Nuetzen
Equestrian Sports and Therapeutic Riding Center of Gold Kraemer Foundation, Frechen
HPZ Wolfgang Fahr Therapeutic Riding Ltd., Ostfildern
Riding Center Children's Aid, Ludwigshafen
Inclusive Equestrian Sports and Therapeutic Riding Center Karlshorst, Berlin
Gut Wittmoldt (estate), Wittmoldt

**Table 2 tbl2:** Requirements for study sites.

Requirements study sites
DKThR-certified facility^a^ [16]
Implementation of hippotherapy according to the guidelines of the DKThR® [15]
Designation of the lead hippotherapist and a coordinator
Appointment of the responsible physiotherapist and his/her deputy
Separate room for baseline, post and follow-up assessments
At least 2 trained therapy horses must be available for the therapy
At least 6 patients must be treatable per week
Comprehensive cooperation with the monitor

a German Curatorship of Therapeutic Riding e.V. (DKThR) represents the national federation for equine-assisted therapy, rehabilitation and equestrian sports for persons with disabilities. The association comprises the fields of medicine, psychotherapy, psychology, education and sport [17].

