### Ethical aspects and monitoring

2.9

The trial will be conducted by researchers of the German Sport University (Cologne, Germany) together with Kamillus Hospital (Asbach, Germany). Study monitoring will be realized by a scientific partner institution (Medical School Berlin Germany(MSB)). It will ensure study quality and compliance with good clinical practice standards (GCP). Furthermore, the study will be designed and conducted in accordance with the German General Data Protection Regulation (GDPR) by the European Union. Unforeseen or adverse events in the therapy process will be documented by the therapists using the German version of the Serious Adverse Event (SAE) Report Form and forwarded to the study team within 24 h [41]. Important protocol amendments will be forwarded to the monitor, ethical committees and if relevant, to the participants directly after decision. Data will be stored on protected servers of the German Sports University Cologne in Germany. Data will be evaluated in a pseudonymized form by assigning a study number to each study participant. A separate list in which the study numbers are assigned to the participant data (name and contact details), as well as the declarations of consent, are only accessible to the leading hippotherapists at the study sites, e.g. to contact the patients as part of the treatment or in the event of revocation during the intervention time. For data analysis, only datasets that are coded with the study number will be processed. The assignment lists will be destroyed after the data collection has been completed and the research data will be destroyed after the usual retention period of 10 years. The included participants have the right to information (including the right to a free copy of the data), as well as correction and restriction of data processing in accordance with the GDPR.

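### One staff group generates the sequence, enrols and assigns under an adaptive scheme, and the arm is assigned before the baseline BBS, so allocation concealment is not assured

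*Protocol article*

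**What the plan says.** All references are to the Protocol article.

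- **Roles** (Screening and randomization): "Scientific study personnel will generate the allocation sequence, enroll participants, and assign participants to interventions based on a stratified adaptive randomization". Candidates first contact the scientific study team, which screens them by telephone with a standard script. A study site physician then examines the patient and gives medical clearance. Assignment follows consent and clearance.
- **Generation and concealment** (same section): "The allocation sequence will be generated by computer-generated random numbers", and "A code-generated random mechanism will be used for concealment". The strata are location, gender and EDSS. The number of EDSS classes, the adaptive rule and its random element are not given.
- **Size** (Design; Study sites): 140 patients, in "two separate study cycles with IG (N = 35) and CG (N = 35) in each study cycle", at 8 sites.
- **Timing** (Table 7): assignment to the study group stands in the registration column. The BBS first appears in the baseline column.
- **Eligibility and analysis set** (Table 4; Statistical procedures): a BBS above 50 before the intervention starts is an exclusion criterion. The primary analysis set (mITT) consists of registered patients who completed the pre-measurement.
- **An available outside party** (Ethical aspects and monitoring): "Study monitoring will be realized by a scientific partner institution".

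**The concern.** Concealment means that whoever decides on a patient's entry, and on its timing, cannot know the arm that comes next. It is normally secured by keeping the people who generate and hold the sequence apart from those who enrol. Here one group is named for generating, enrolling and assigning. A code hides nothing from the people who produce it. Under an adaptive scheme the next assignment also depends on the earlier ones, which the same group handles.

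If the next arm is known or guessable, a patient's entry can be brought forward, delayed or discouraged according to that arm. The result is selection bias. The planned covariates (facility, gender, age, baseline BBS, EDSS) adjust for selection on those measured factors, but not for selection on motivation or expected adherence. Patients and therapists cannot be blinded to hippotherapy, so a preference for one arm is plausible.

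The order in Table 7 opens a second route. If the BBS is first taken after assignment, both the exclusion for a BBS over 50 and membership of the mITT set depend on events after the arm is known.

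**Working it through.** **1. Roles against safeguard.** The article names one group for all three tasks. Its concealment sentence describes a way of producing codes. It names no custodian, no central service and no limit on access. The statement about roles is positive text, so the point does not rest only on detail left out of a condensed article.

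**2. How predictable could allocation be?** The article speaks both of a computer-generated sequence and of an adaptive scheme, so both families of rule were tried.

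Inputs from the article: 140 patients, 1:1, 8 sites, two genders, EDSS 4 to 6, two cycles of 70.

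Assumptions: equally likely sites, a 70/30 gender split, 2 or 5 equal EDSS classes, and either a restart of the scheme at cycle 2 or none. There were 1,000 simulated trials per scenario. The observer is assumed to know the rule, the earlier allocations and the new patient's strata.

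| Rule | Allocations fully determined | Best guess right |
|---|---|---|
| Minimisation, no random element | 77–79% | 89% |
| Minimisation, preferred arm with probability 0.8 | 0% | 75% |
| Stratified blocks of 2 | 28–44% | 64–72% |
| Stratified blocks of 4 | 5–24% | 57–66% |
| Next allocation hidden | 0% | 50% |

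For minimisation without a random element and for blocks of 2, the two columns are linked by: guess right = determined + (1 − determined)/2. For minimisation with 2 EDSS classes and a restart, 0.776 + 0.224/2 = 0.888. For blocks of 2 in the same setting, 0.389 + 0.611/2 = 0.695.

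**3. Do small strata drive this?** Number of cells = sites × genders × EDSS classes.

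- 2 classes: 8 × 2 × 2 = 32 cells; 140/32 = 4.4 patients per cell, and 70/32 = 2.2 per cycle.
- 5 classes: 8 × 2 × 5 = 80 cells; 140/80 = 1.75 per cell, and 70/80 = 0.9 per cycle.

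Cells are small in both cases. But going from 2 to 5 classes with a restart lowered the rate of right guesses under blocks of 2 (69.5% to 63.8%) and blocks of 4 (62.7% to 56.7%). Under minimisation it hardly moved (88.8% to 88.6%). Small strata are not the source of predictability. Access to the rule and to the running balance is.

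**4. Order of events.** Table 7 gives registration (eligibility, consent, clearance, assignment), then baseline (first BBS). Table 4 excludes on the BBS. The mITT definition requires the pre-measurement. Read together, a patient can be assigned, learn the arm, and then be excluded on the BBS or fail to attend baseline. In either case the patient may be missing from the primary analysis.

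**The case against.** The strongest reply is that foreseeability is a risk and not a shown fact. The group named is a collective and may consist of different people with different access. The same section says that a concealment mechanism is used. The custodian, the access rights and the rule are details that an article may leave to the full protocol. A site physician's examination and clearance stand between the telephone call and assignment. The Design section also allows that a cohort is assigned together before therapy begins, in which case knowing the next patient's arm matters less. The BBS is rated by blinded assessors, controls are offered later sessions, and several covariates are adjusted for.

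Much of this stands. Three stronger readings are tempting, and the article does not support them:

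- **That a large share of assignments is in fact predictable.** The determined share in the scenarios runs from 0% to 79%, depending on a rule that the article does not give.
- **That the many small strata cause the predictability.** Finer strata lowered it or left it unchanged.
- **That the team alone decides entry by telephone.** The call is a first screen, and clearance and consent come after it.

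The reply does not remove the core. The physician's clearance limits who may enter, but it does not hide the next arm from the team that screens and schedules. Blinded rating guards against detection bias, not selection bias. Covariate adjustment reaches only measured factors. A BBS might be taken at the clearance examination, but Table 7 lists none there.

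**Conclusion.** The concern holds in a limited form. As described, one staff group generates, enrols and assigns under an adaptive scheme, and the stated mechanism does not by itself hide the next allocation from that group. Concealment is therefore not assured, though no breach is shown. For an observer with full access, the best guess would be right in 57% to 89% of cases across the rules tried. With proper separation of roles it would be 50%. These figures rest on assumed rules, assumed EDSS classes and an assumed patient mix. The resulting bias in the BBS difference cannot be computed from the article.

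The order in Table 7 makes the point weightier, because entry to the primary analysis set can be settled after the arm is known. For a trial that calls itself confirmatory, this should be corrected.

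**What to change.** For all remaining allocations:

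1. A person or existing partner outside recruitment and assessment, for example the monitoring institution, generates and holds the algorithm, which includes a random element.
2. Each assignment is released only after consent, eligibility and baseline data, including the BBS, have been entered irrevocably. Table 7 is changed to place assignment after the baseline assessment.
3. Recruiters and BBS assessors have no access to the algorithm or to the running balance.

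For allocations already made, document who generated the sequence, who could see it or the arm totals, and whether the BBS was taken before or after assignment.

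The cost is protocol wording plus a script or web form at a partner already in the trial. The downside is that each patient's assignment must be returned within a short turnaround. No eligibility threshold or treatment rule changes.
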